## Abstract

**Background:**

Acute exacerbations of chronic obstructive pulmonary disease (eCOPD) are a major clinical challenge, often leading to frequent emergency room visits and significantly reducing patients’ quality of life. Early detection through wearable devices could facilitate timely interventions at the community level, reducing hospital admissions and disease-related morbidity and mortality.

**Objective:**

This study seeks to retrospectively assess the feasibility and reliability of the Frontier X2 wearable device for continuous monitoring of clinically relevant physiological signals in volunteers with chronic obstructive pulmonary disease (COPD) who experience acute exacerbations. In particular, the study aims to characterize early physiological alterations that may occur prior to the exacerbation of COPD, assessing the ability of the device to capture these changes in the real-world settings.

**Methods:**

This single-center feasibility study involves prospective physiological data collection with retrospective analytical evaluation of physiological changes occurring around clinically confirmed COPD exacerbations. A total of 30 participants with COPD (Modified Medical Research Council Grades 1‐4) who have experienced at least one exacerbation within the past 12 months will be included. Each participant will wear a continuous physiological monitoring device in their free-living environment for up to 18 months or until an eCOPD event occurs. The device will continuously collect physiological signals, including heart rate, respiratory rate, and heart rate variability. Data will be analyzed using statistical quality control methods, specifically the Cumulative Sum approach, to identify physiological deviations occurring within 7 days (168 h) prior to an exacerbation event. These findings will be correlated with clinical records and qualitative data. Qualitative information will be obtained through biweekly self-administered questionnaires assessing symptom changes and through additional adherence and usability questionnaires completed during home visits conducted every 2 weeks by the researcher.

**Results:**

Recruitment for this study started in June 2024 and was completed in July 2025. It is anticipated that data collection will be completed within 18 months of study initiation, with data analysis finalized by December 2025. Final results will be published in January 2026.

**Conclusions:**

The BREATH-TRACHER 2 study will evaluate the use of the Frontier X2 device in participants with COPD in home settings. The Frontier X2 device, if successful, has the potential to transform COPD management and support proactive care, leading to enhanced clinical outcomes and reduced disease mortality and morbidity.

## Introduction

### Background

Chronic obstructive pulmonary disease (COPD) represents a significant public health challenge, with individuals often enduring the disease for many years [1]. It ranks among the top three leading causes of death globally, responsible for 3.23 million deaths in 2019 [2], and the United Kingdom has the third highest COPD mortality rate in Europe [3]. Projections suggest that by 2060, annual global deaths attributable to COPD will exceed 7 million [4].

In the United Kingdom, the burden is equally concerning. In 2019, approximately 21,000 COPD-related deaths were reported [5], while more recent estimates indicate that COPD claims around 30,000 lives annually in the United Kingdom [6]. Currently, 1.4 million people in the United Kingdom are diagnosed with COPD, a figure that has risen steadily over the past decade [7] and is projected to be 1.62 million by 2040 [8]. Each year in the United Kingdom, around 115,000 people are newly diagnosed with COPD, equating to a diagnosis occurring every 5 minutes [3].

Globally, the World Health Organization estimates that 64 million people are living with COPD [9]. In the United Kingdom, the economic burden of the disease is of major concern. Annual management costs to the National Health Service (NHS) are estimated at £1.9 billion (US $3.13 billion) [10], and COPD accounts for 29% of all respiratory disease–related health care expenses, as shown in Table 1. Given that the total cost of respiratory diseases has been estimated at £165 billion (US $271.6 billion), COPD alone contributes approximately £48 billion (US $79 billion) to this burden [10].

**Table 1. T1:** Economic burden of COPD and total lung conditions in the United Kingdom, based on 2014 estimated data^a^.

	Annual expenditure (£m)	
Category	COPD expenses	Total lung conditions
Direct costs	1847	9895
Indirect costs	61	1222
Intangible costs	46,636	154,241
Total economic burden in the United Kingdom	48,545	165,357

a Adapted from [10].

Emergency hospital admissions constitute the largest share of COPD-related costs, representing 72.8% of the total, while prescription medications account for 12.2% [11]. Exacerbations further intensify the economic impact, with moderate episodes costing approximately £118 and severe episodes ranging between £3,329 and £3,726 across UK territories [12,13].

The overall yearly direct health care expenses for individuals with COPD in England, which encompass the costs of moderate and severe exacerbations as well as maintenance, were projected to rise from £1.50 billion in 2011 to £2.32 billion by 2030 [12]. This data highlights the urgency for innovative health care models focused on early intervention and the prevention of exacerbations.

The clinical course of COPD is marked by chronic respiratory symptoms, airflow limitation resulting from airway or alveolar abnormalities, and exacerbations, which are pivotal events in disease progression [14]. These exacerbations, defined by the Global Initiative for Chronic Obstructive Lung Disease, involve an acute worsening of respiratory symptoms beyond typical day-to-day variation. They are often triggered by bacterial or viral infections, environmental factors like air pollution or weather changes, and occasionally by unknown factors [1]. Exacerbations significantly impact patient outcomes, including increased hospitalization rates, a decline in quality of life, and heightened mortality risks [15,16]. Moreover, exacerbations serve as indicators of disease progression and predictors of future health outcomes [17].

Unreported exacerbations remain a persistent challenge in COPD management, often influenced by factors such as age, gender, and socioeconomic status [18]. The failure to report these events leads to undertreatment, prolonged recovery, and diminished quality of life while also underestimating the patient’s risk of subsequent exacerbations. Treatment delays further exacerbate outcomes, with research indicating a median delay of 4.8 days from onset of an exacerbation to recognition, 9.3  days from recognition to action, and 8.3  days from recognition to general practitioner (GP) visit [19]. Early treatment is associated with faster recovery, reduced hospital admissions, and improved health-related quality of life, highlighting the importance of prompt medical intervention and patient education regarding exacerbation symptoms [20]. The management of acute exacerbations of COPD emphasizes the significance of effective disease management, which includes implementing a self-management plan that features a self-administered rescue pack containing antibiotics and steroids [21]. However, there is currently a limited understanding of patient self-management and appropriate use of the rescue pack. This often results in improper medication usage, delays in treatment, and instances of both overuse and underuse of medications [21,22].

Preventing hospital readmissions is a key strategy in alleviating the overall burden of COPD. Understanding the physiological changes that occur during exacerbations is essential for improving disease management. Studies show that some physiological signals begin to change before an overt clinical exacerbation, providing an opportunity for earlier detection and intervention [23,24]. Continuous monitoring of vital signs also has the potential to reduce the frequency and severity of exacerbations. However, earlier studies have encountered limitations such as small participant samples, potential conflicts of interest, and the complexity of monitoring devices that require frequent and precise usage [25]. Although advancements in wearable technologies have improved accessibility for continuous vital sign monitoring, their accuracy and reliability remain a cause for concern [26].

The BREATH-TRACHER 2 study aims to utilize the Frontier X2 wearable device to detect early indications of exacerbations of COPD (eCOPD). The aim is to identify physiological changes sooner than otherwise feasible, which could help reduce hospitalizations and alleviate the overall burden of the disease. By monitoring heart rate (HR), breathing rate (BR), and other physiological parameters in individuals with COPD, this study aims to assess whether early signal changes can be detected prior to a clinical exacerbation. Earlier identification may support timelier treatment and could potentially reduce the impact of exacerbations in future applications.

In the literature, several studies have investigated the use of wearable technologies to detect eCOPD using physiological parameters such as HR, BR, and HR variability (HRV). These parameters have shown promising potential as early indicators of eCOPD. However, most previous studies have relied on photoplethysmography or accelerometer-based technologies, which are more susceptible to motion artifacts, environmental noise, and signal interruptions—particularly in free-living conditions. While the goal of these studies was to enable remote, real-world monitoring, the accuracy of photoplethysmography and motion-based sensors can be significantly affected by such external factors.

Remote monitoring technologies are increasingly used for the diagnosis, treatment, and tracking of disease progression across a wide range of conditions. They can be evaluated and compared according to factors such as predictive accuracy, cost, usability, patient comfort, and physical design [26]. Some earlier studies have employed bulky or portable systems that are unsuitable for continuous monitoring in daily life, whereas lightweight, user-friendly devices are better suited for long-term free-living applications and can improve adherence and data quality. Device cost is also a key consideration for large-scale clinical deployment.

The Frontier X2 device used in this study operates using continuous single-lead electrocardiography (ECG) technology, which measures the heart’s electrical activity through electrodes embedded in a chest strap. The device records the depolarization and repolarization of cardiac muscle during each heartbeat, producing high-fidelity HR and BR signals derived directly from the ECG waveform. The system automatically filters noise from muscle movement and other artifacts, ensuring stable data capture. Frontier’s proprietary software detects R-peaks and provides raw respiratory rate (RR) intervals, from which HRV parameters such as the SD of normal-to-normal intervals can be calculated. Owing to its lightweight design (approximately 20 g), continuous data collection capability, and relatively low cost, the Frontier X2 represents a practical and reliable option for long-term physiological monitoring in COPD populations.

### Rationale for Study and Potential Impact

The rationale of the study is to address the need for earlier identification of an acute exacerbation in people with COPD and to explore the potential of remote monitoring using a Frontier X2 wearable device to monitor changes in RR and cardiac signals (HR and HRV).

Detecting exacerbations at an early stage is crucial as timely intervention and appropriate management can prevent severe exacerbations and their associated complications. By utilizing a wearable device for remote monitoring, the study aims to continuously collect physiological signals from patients with COPD during their daily activities. This approach offers the opportunity to monitor patients in their natural environment and capture subtle changes that may indicate disease progression or exacerbations before they are clinically conspicuous.

### Aims and Objectives

#### Aims

The study aims to establish whether the Frontier X2 wearable device is suitable to monitor the clinical health of a person with COPD and immediately identify when it begins to deteriorate. Earlier notification of disease worsening could improve rate of patients seeking therapy at a community level and reduce likelihood of hospital admission. Additionally, a wearable device could provide real-world insights into the effectiveness of regular prescribed medications and measure the impact of any rescue interventions.

#### Primary Objective

The primary purpose of the study is to retrospectively establish if the Frontier X2 medical device can accurately identify when a person with COPD is starting to experience a clinical exacerbation.

#### Secondary Objectives

The secondary objectives of this study are to (1) explore if the device can monitor volunteer compliance of their inhaler usage; (2) explore instances of signal-clinical discordance (ie, situations where physiological patterns captured by the device do not fully align with the clinically documented eCOPD event); (3) explore if the device can stratify disease severity in individual volunteers; (4) explore if the device can identify responsiveness to intervention treatment following a COPD exacerbation; (5) assess device adherence, usability, and comfort;, and (6) explore how soon the device can identify when a person with COPD is starting to experience a clinical exacerbation.

## Methods

### Overview

An eCOPD refers to an acute worsening of dyspnea, cough, and sputum production occurring within a 14- day period. It may also present with tachypnea and tachycardia and is commonly associated with local or systemic inflammatory responses triggered by respiratory infections, environmental pollutants, or other irritants affecting the airways [1]. eCOPD is considered a sign of disease progression, a predictor of future health and outcomes, and a leading cause of morbidity and mortality, and it increases disease costs [17]. Early identification and timely reporting of symptom deterioration are therefore essential to minimize hospitalization and reduce disease burden, underscoring the importance of reliable exacerbation detection in patients with COPD.

Building on this rationale, this study adopts a mixed methods, observational, open-label, uncontrolled cohort design with prospective physiological data collection and retrospective analytical evaluation to explore the feasibility and potential of continuous physiological monitoring for detecting early changes of eCOPD. Participants will be continuously monitored throughout their participation in the study, including before, during, and after their COPD exacerbation using a wearable device that records physiological signals. The 168-hour pre-exacerbation period and the subsequent return-to-baseline period after the event will be retrospectively examined using the physiological data captured by the device. COPD exacerbation will be identified and cross-validated from information provided by participants via individual COPD symptom questionnaires and cross-validated through clinical records in the participants’ GP electronic medical system. The study aims to recruit 30 volunteers who have previously experienced COPD exacerbation-induced hospitalization within a 1-year period prior to recruitment.

There is no specific medical intervention planned as part of the study; participants will continue to receive their usual standard of care throughout the study period. However, wearing a medical monitoring device may lead to behavioral changes (Hawthorne effect) among participants, such as increased disease awareness or improved adherence to medication (eg, inhaler) use. These potential behavioral effects are acknowledged as possible outcomes of the monitoring process.

### Primary and Secondary End Points

#### Primary End Point

The primary end point is the retrospective analysis of physiological signals following a clinically validated COPD exacerbation. Exacerbations will be confirmed via the electronic GP system, either upon hospital admission or when managed at home using a prescribed rescue pack.

We will retrospectively analyze physiological data to identify the earliest point at which alterations in signals become detectable prior to a clinically confirmed exacerbation. The analysis will continue until the participant’s signals return to baseline. This window is expected to span approximately 7 days (168 h); both the timing and duration of physiological deviations may vary depending on device sensitivity and the nature or severity of the exacerbation, and these variations will be examined descriptively. This study aims to investigate these pre-exacerbation physiological alterations and evaluate the potential of the wearable device to detect these early changes, potentially supporting future clinical monitoring and management in individuals with COPD.

#### Secondary End Points

The secondary end points are to (1) evaluate the everyday usability of the wearable device in a primary care setting; (2) appraise the ability of the wearable device to monitor daily disease burden and impact of regular medication use on the long-term health management of a person with COPD; (3) determine the potential of the wearable device to assess the effectiveness of any clinical intervention provided during an exacerbation.

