#### Quantitative Analysis

Time-series analysis will be conducted on physiological data to identify patterns and trends over time. Statistical software including SPSS, Minitab, and Python will be used for data processing and analysis. Control chart techniques, particularly the Cumulative Sum (CUSUM) chart, will be applied to evaluate physiological changes before, during, and after COPD exacerbations. The adequacy of the selected time-series models will be assessed through autocorrelation analysis and examination of residual distributions to ensure accurate representation of the underlying data structure.

Physiological parameters, including HR, HRV, and its derived metrics—the root mean square of successive differences, the SD of normal-to-normal intervals, low-frequency power, high-frequency power, and the low-frequency to high-frequency ratio—as well as RR, will be used for quantitative analysis. As this feasibility study is conducted in free-living conditions, it is not possible to fully control contextual factors that may influence HR, RR, or HRV, such as medication changes, intercurrent infections, sleep variability, or changes in daily activity. These factors will therefore be documented during biweekly follow-up visits and reviewed descriptively when interpreting physiological deviations. Analyses will focus on within-participant deviations from each individual’s baseline rather than between-participant comparisons.

The CUSUM chart approach will follow methodologies previously described by Montgomery [31], which enables detection of small, sustained deviations from baseline values in time-series data. For each participant, baseline data will correspond to a stable period with no reported symptom worsening—specifically, the first 7 days of participation. The reference value (k) and decision threshold (h) will be individually calculated based on this baseline period. In accordance with the inclusion criteria, all participants must have been free from any eCOPD events for at least 6 weeks prior to recruitment, supporting the selection of the initial stable days as an appropriate baseline.

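### Secondary end point 2 and the Aims speak of the impact or effectiveness of regular medication on long-term health management, which an uncontrolled, event-truncated cohort already on treatment cannot identify

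*Protocol article*

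**What the plan says.** Under Secondary End Points, the second item is to judge how well the device can "monitor daily disease burden and impact of regular medication use on the long-term health management of a person with COPD". The Aims add that a wearable could give "real-world insights into the effectiveness of regular prescribed medications". None of the six Secondary Objectives concerns the effect of maintenance treatment: the first is about inhaler compliance and the fourth about response to treatment after an exacerbation.

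The Overview describes a "mixed methods, observational, open-label, uncontrolled cohort design" with no planned medical intervention, in which "participants will continue to receive their usual standard of care throughout the study period". It also accepts that wearing the device may change behaviour, "such as increased disease awareness or improved adherence to medication (eg, inhaler) use".

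In Quantitative Analysis, baseline is each person's first 7 days of participation. "Analyses will focus on within-participant deviations" from that baseline, not on comparisons between participants. The same section lists contextual factors that cannot be fully controlled, "such as medication changes, intercurrent infections, sleep variability, or changes in daily activity". These are noted at the 2-weekly visits and considered descriptively. Study Assessments makes medication usage one item of the 2-weekly symptom questionnaire.

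The article is not consistent on the length of observation. The Abstract (up to 18 months or until an event) and Quantitative Analysis (collection stops once the GP record confirms an event) end it at the exacerbation. The Overview and the Primary End Point carry it on afterwards until signals return to baseline.

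**The concern.** An impact of regular medication is a comparison: health with the treatment against health without it, or under a different amount of it. The study plans no such comparison and names no long-term outcome on which the impact would be seen. Medication also has two roles. It is the subject of an end point, and in the analysis section it is one of several disturbing factors to bear in mind when reading the charts. The article states no analysis that separates these roles.

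What is at stake is the conclusion the study may draw. With the present wording, a steady chart in a treated participant could be reported as evidence that maintenance treatment works, or a drifting one as evidence that it does not. The data would support neither statement.

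**Working it through.** **1. What the baseline does to a medication effect.** Write the signal of person *i* at time *t* as Y(i,t) = a(i) + m·M(i,t) + d(i,t) + error. Here M is regular medication use, m its effect and d the state of the disease. The charted quantity is the deviation from the first 7 days, at time 0:

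Y(i,t) − Y(i,0) = m·[M(i,t) − M(i,0)] + [d(i,t) − d(i,0)] + error.

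- If medication use is constant, the first bracket is zero and m disappears.
- If medication use changes, the first term remains, but it is added to the change in disease. Where medication changes because the patient is getting worse, the two brackets move together. Nothing in the design separates them: there is no comparison group, planned switch, or period before or off treatment.

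**2. How long people are observed.** The inputs are 0.5 to 3 exacerbations per person-year, 18 months of follow-up and 30 participants (Patient Population Size), with enrolment from June 2024 to July 2025 and collection ending in December 2025 (Results).

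The article's own figures come first: 0.5 × 1.5 = 0.75 and 3 × 1.5 = 4.5 expected events, as stated. With a constant hazard r (my assumption):

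- probability of at least one event in 18 months = 1 − exp(−1.5r). The article's figure of 70% needs r = −ln(0.30)/1.5 = 0.80 per year, so it fits most of the cited range but not its lower end.
- mean time observed, if collection ends at the event = [1 − exp(−rF)]/r, where F is the time available.

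The calendar gives F = 18 months for the first entrant and about 5 months for the last. The final column averages over F from 5 to 18 months, assuming even enrolment.

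| Rate per year | Expected events, 18 months | At least one event | Mean months observed, F = 18 | Mean months observed, F = 5 to 18 |
|---|---|---|---|---|
| 0.5 | 0.75 | 52.8% | 12.7 | 9.0 |
| 0.8 | 1.2 | 69.9% | 10.5 | 7.8 |
| 1 | 1.5 | 77.7% | 9.3 | 7.2 |
| 2 | 3.0 | 95.0% | 5.7 | 4.9 |
| 3 | 4.5 | 98.9% | 4.0 | 3.7 |

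Even with 18 months available to everyone, the share still under observation at 12 months, exp(−r), runs from 61% at 0.5 per year to 5% at 3 per year. Those who worsen soonest contribute the least time.

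**3. How often the reference is measured.** Heart rate, breathing rate, HRV and step count are recorded continuously (Monitoring). Symptoms and medication use are recorded every 2 weeks. Mean observation of 9.0 to 3.7 months is 9.0 × 52/12 = 39 weeks down to 3.7 × 52/12 = 16 weeks. That is about 20 down to 8 questionnaires per person if none is missed.

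**The case against.** The strongest reply is that the end point asks only what the device is able to monitor, in a feasibility study, and that the Aims sentence is conditional. A descriptive appraisal, including a negative one, is therefore possible. This stands, and it is why the remedy is a rewording. It does not rescue *impact*: to judge whether a device tracks the impact of a medication, that impact must be identifiable from something, and here it is not.

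A reader might go further than the text allows in four ways.

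- *Care is unchanged, so no contrast exists at all.* The article never says care is unchanged. It expects medication changes and better adherence, and it records medication use. The accurate statement is that there is no planned contrast. Only a constant effect cancels.
- *Daily burden rests on the 2-weekly questionnaire alone.* The device supplies daily signals. It is the symptom reference that is sparse.
- *Follow-up certainly stops at the first event.* The article contradicts itself here, and also provides for more than one event per person. Event-free participants may be followed for up to 18 months.
- *The authors will misread their charts.* Nothing says so, and medication changes are to be considered in interpretation. The risk comes from the wording of the end point.

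A fuller protocol or analysis plan may specify the secondary analysis, so absence of a model is not a criticism. No such plan can add a contrast or a long-term outcome that the study does not collect.

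**Conclusion.** The concern holds as a matter of what may be concluded. The effect of regular medication on long-term health management is not identifiable from this design, whatever the device records. That rests on the uncontrolled cohort, the on-treatment baseline, the absence of any planned treatment change and the lack of a named long-term outcome. It needs no sample-size figure.

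The observation times add to the point but are conditional: about 9.0 to 3.7 months on average, given constant hazard, even enrolment and collection ending at the event. If monitoring instead continues to recovery, the extra data concern recovery from the exacerbation, which is end point 3, so the conclusion is the same.

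The variation in medication use that does occur can support description only. The primary end point is unaffected. This is a secondary end point whose wording should be corrected before results are reported.

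**What to change.** 1. In Secondary End Points, remove *impact* and *long-term* from item 2. In the Aims, remove the claim about the effectiveness of regular medication.
2. Restate item 2 as an exploratory, descriptive, within-person association between the 2-weekly symptom score (and recorded medication use) and device heart rate, respiratory rate and HRV over the preceding days. One suitable analysis is a mixed model with a participant random effect and person-mean centring, so that the estimate reflects change within a person. State that no causal claim about medication will be made, and that the symptom reference is 2-weekly.
3. Reconcile the statements on whether data collection ends at confirmation of the event (Abstract, Quantitative Analysis) or continues until return to baseline (Overview, Primary End Point).

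The cost is rewording in two places, one reconciliation and one model on data already being collected. The downside is a narrower claim.
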